### 8.1 Data Recording (CRF/eCRF)

### 8.2 Trial Folders

The trial folders should contain the complete documentation of the trial. They should allow the evaluation of the conducted trial and data quality.

### 8.2.1 Trial Master File (TMF)

The paper-based/electronic TMF, established at the beginning of the trial and secured in a safe place, contains all essential documents that demonstrate that the trial is conducted in accordance with regulatory requirements and ICH GCP. All documents will be maintained and updated as appropriate throughout the trial. Previous versions of the documents must be retained in the TMF and will be clearly labelled as outdated or will be relocated in a section for outdated documents. The TMF is archived at the end of the study for 15 years.

### 8.2.2 Investigator Site File (ISF)

The paper-based/electronic ISF, established at the beginning of the trial will be secured in a safe place (the file is provided to the site at the site initiation visit). It contains all essential documents maintained by the PI(s). All documents will be maintained and updated as appropriate throughout the trial. Previous versions of the documents must be retained in the ISF and will be clearly labelled as outdated or versions will be relocated in a section for outdated documents. Within the Monitoring, the ISF will be checking regarding actuality and completeness in accordance with the formalities. After completion or discontinuation of the study this ISF has to be kept for 15 years.

## 8.3 Data Storage

### 8.3.1 Storage duties of the Sponsor

The Sponsor has to keep all study-relevant documents of the completed or discontinued clinical trial after completion or discontinuation of the study for a minimum of 15 years.

### 8.3.2 Storage duties of the Investigator

The Investigators have to keep all records and documents, which are related with the study or the allocation of investigational medicinal products (e.g. data entry form, consent form, list of the allocations of investigational medicinal products and further relevant documents), for a minimum of 15 years.

Medical records and other original data have to be kept for 30 years.

## 9. Data Management

The protocol has been reviewed from a database designing perspective, for clarity and consistency. The entries made in the CRF will be monitored by the Clinical Monitor for completeness and filled up CRFs are retrieved and handed over to the CDM.

Discrepancies are either flagged to the investigator for clarification or closed in-house by Self-Evident Correction (SEC) in case of obvious spelling errors. For discrepancies that require clarification from the investigator, Data Clarification Forms (DCF) will be sent to site. Investigators will write the resolution or explain the circumstances that led to the discrepancy

in data within a given time period. When a resolution is provided by the investigator, the same will be updated in the database by the CDM. The resolved data discrepancies are recorded as „closed“. In cases, where the investigator will not be able to provide a resolution for the discrepancy, they will be considered as „irresolvable“ and will be updated in the discrepancy database.

## 10. Protocol Deviations

All deviations to the study protocol have to be documented with an explanation. Deviations have to be reported to the sponsor, who is responsible for their valuation.

Reasons for trial termination of a patient have to be documented. In case of termination for safety reasons or insufficient effect of the IMP, the patient has to be further monitored.

Deviations have to be analyzed whether changes of the clinical investigation plan or the closure of the study are necessary.

If necessary, the ethics committee or the responsible authorities have to be informed.

Please define instructions for documentation, report and analysis of protocol deviations.

Requirements for reporting including time frame.

Corrective and preventive measures and criteria for the exclusion of a principal investigator.

## 11. Statistics

### 11.1 Sample Size

The sample size is generated for the primary endpoint of a superiority testing of level of neutralizing antibodies against the B.1.351 variant between the two randomized study arms (arm 1: ChAdOx1-S prime & boost, arm 2: ChAdOx1-S prime and BNT162b2 boost). A comparison against arm 3 (BNT162b2 prime & boost) is exploratory and will be done descriptively.

In a study of Madhi  92% of participants showed neutralizing antibodies following vaccination with ChAdOx1-S prime & boost against the B.1.1.7 (British) variant and 58% against the B.1.351 (South African) variant. Focusing on the improvement of the heterologous vaccination with the Biontech boost against the South African variant with regard to primary the endpoint of neutralizing antibodies we consider a sample size of n=1000 per study arm as appropriate. With this sample size, we can detect an increase in the percentage of participants with neutralizing antibodies against the South African variant from 58% to 65.5% as statistically significant, with a power of >90% and alpha of 5%. If the increase is 10% the statistical power would be >99%.

For the secondary endpoint of efficacy against breakthrough infection with the B.1.351 variant, based on the current number of 8 new cases per week in Tyrol with the B.1.351 variant we expect 208 cases during the next 180 days with no change in rate of infection.

Currently, the B.1.351 is concentrated in 4 districts – Kufstein, Schwaz, Innsbruck Land and Innsbruck Stadt giving a total population of 416,758, this gives a rate of 49,9/100,000 people in 180 days. As not all cases are sequenced we estimate that only 5% of B.1.351 variants are detected, this would mean in total a rate of approximately 1000 cases per 100000 population of the B.1.351 variant would occur over 180 days – this means 10 cases per 1000. This scenario could lead to 10 cases in the ChAdOx1-S prime & boost arm (Arm 1) and 0 case in the ChAdOx1-S prime and BNT162b2 boost arm (Arm 2). In the extreme situation that all 10 cases occur in Arm 1, this would be statistically significant. However, due to the decreasing infection rates in Tyrol we would currently consider this an underpowered analysis and as such would perform a posthoc power analysis. In addition, a second immune escape variant, B.1.1.7.+E484K has recently occurred in Tyrol with over 900 cases until now. However, the development of this outbreak is currently not predictable.

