| Statistical methods & analyses | 
An interim analyses applying the Haybittle Peto rule for early stopping had been applied. Safety and efficacy have been analyzed on day 30 after n=200 patients had been randomized. level of neutralizing antibodies (primary endpoint) had been significantly lower in the homologous Vaxzevria arm compared to the heterologous (p-value < 0.001) this arm had been stopped. Already recruited participants in all arms will be further followed for durability of antibody response and the number of breakthrough infections. New participants in the two remaining arms are recruited with the aim to recruit up to 1000 participants in each of these two arms to analyse the number of breakthrough infections. Efficacy analysis will employ contingency table analysis,
                                                                                                                                                                                                                                                                   |

|  |                                                                                                          |
|--|----------------------------------------------------------------------------------------------------------|
|  | chi-square testing and a logistic regression adjusting for the stratifying variables study site and sex. |
|--|----------------------------------------------------------------------------------------------------------|

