## 4.1 Number of Patients

A total of 2124 subjects will be included in this study. Each arm of 1000 subjects will be vaccinated as it follows:

Group A: ChAdOx1-S prime and BNT162b2 boost

Group B: BNT162b2 boost prime and BNT162b2 boost

Group C: ChAdOx1-S prime and ChAdOx1-S boost (this arm has been closed after 124 subjects have been randomized to; therefore, the total number of subjects is reduced from 3000 to 2124).

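### Section 11.1 was not updated when the homologous Vaxzevria arm closed at 124: it justifies a finished comparison and gives no power or precision for the breakthrough comparison (A versus B) now being recruited for

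*Protocol*

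**What the plan says.** Section 11.1 bases the sample size on "superiority testing of level of neutralizing antibodies against the B.1.351 variant between the two randomized study arms", that is Arm 1 (Vaxzevria twice, Group C) against Arm 2 (Vaxzevria then Comirnaty, Group A). It concludes "we consider a sample size of n=1000 per study arm as appropriate". It claims detection of a rise "from 58% to 65.5% as statistically significant, with a power of >90% and alpha of 5" per cent, and adds "If the increase is 10% the statistical power would be >99" per cent. It describes the comparison with Arm 3 (Comirnaty twice, Group B) as exploratory and descriptive.

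For breakthrough infection, 11.1 derives about 10 B.1.351 cases per 1000 over 180 days and then writes "This scenario could lead to 10 cases in the ChAdOx1-S prime & boost arm (Arm 1"), with none in Arm 2. It calls this analysis underpowered because infection rates in Tyrol are falling, and says the team "as such would perform a posthoc power analysis".

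Other sections describe a changed trial. Section 4.1 says of Group C that "this arm has been closed after 124 subjects have been randomized to", with the total cut from 3000 to 2124. The Synopsis says that the remaining two arms are to recruit "up to 1000 participants in each of these two arms to analyse the number of breakthrough infections", and section 1.3 names the contrast as homologous Comirnaty against the heterologous group.

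**The concern.** A sample size section should tell the reader what the planned enrolment can show. Here the only calculation concerns an antibody comparison that has already been decided at the interim. The recruitment still under way serves a different endpoint (infection rather than antibody response) and a different contrast (A versus B rather than A versus C). The figure of 1000 per arm has been carried over without a new rationale.

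At stake is whether anyone reading 11.1 can judge what up to 2000 people in A and B, with weekly testing and repeated blood draws, will reveal about breakthrough infection. If the result shows no clear difference, the plan offers no prior statement of how large a difference could have been missed. Its proposed substitute, a power calculation after the data are in, cannot supply that.

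**Working it through.** **1. The plan's antibody figures.** Inputs from 11.1: 58% versus 65.5%, 1000 per arm, alpha 5%. Section 11.3.5 makes tests two-sided.

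Power = Φ{(|p1−p2| − 1.96·SE0) / SE1}, with SE0 = √[2p̄(1−p̄)/n] and SE1 = √[p1(1−p1)/n + p2(1−p2)/n].

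- 58% v 65.5%: SE0 = 0.02173, SE1 = 0.02167; (0.075 − 0.0426)/0.02167 = 1.50; power 93.3%. Stated as above 90%: reproduces.
- 58% v 68%, reading the 10% as percentage points: power 99.6%. Stated as above 99%: reproduces.
- Section 11.3.3 adds Haybittle-Peto looks at 200 and 400 randomized, at p<0.001. A simulation of 58% v 65.5% with those looks and a maximum of 1000 per arm gives 93% power, so the looks cost nothing material.

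**2. The plan's breakthrough scenario.** 8 cases per week × 26 weeks = 208. 208/416,758 = 49.9 per 100,000. Divided by the assumed 5% detection, this is 998 per 100,000, or about 10 per 1000. For 10/1000 v 0/1000, Fisher p = 0.0019. All of this reproduces with 1000 in Arm 1.

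With the actual 124 in that arm:
- Expected cases = 124 × 0.01 = 1.24.
- Probability of no case = 0.99^124 = 29%.
- Ten cases would need a risk of 10/124 = 8.1%, about eight times the plan's rate.

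**3. What 1000 per arm gives for A versus B.** The protocol states no figure, and no all-variant breakthrough risk from which to derive one. The 180-day risks below are therefore assumptions. Power uses the formula in step 1.

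- 1% v 2%: SE0 = 0.005436, SE1 = 0.005431; (0.010 − 0.01065)/0.005431 = −0.12; power 45%.
- 2.5% v 5%: SE0 = 0.008496, SE1 = 0.008478; (0.025 − 0.01665)/0.008478 = 0.985; power 84%.

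For equal observed risk p in both arms, the 95% limits for the risk ratio are 1 divided and multiplied by exp{1.96·√[2(1−p)/(1000p)]}. For 10 v 10 cases: exp(1.96 × √0.198) = 2.39, so 0.42 to 2.39.

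| Assumed 180-day risk | 95% CI for the risk ratio if risks are equal | Higher risk detectable with 80% power (risk ratio) |
|---|---|---|
| 0.5% | 0.29 to 3.44 | 1.85% (3.7) |
| 1% | 0.42 to 2.39 | 2.7% (2.7) |
| 2% | 0.54 to 1.85 | 4.2% (2.1) |
| 5% | 0.68 to 1.47 | 8.1% (1.6) |

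No dropout is allowed for, so actual precision would be somewhat lower.

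**4. Post-hoc power.** Power computed at the observed difference is a function of the p-value alone: a result just at p = 0.05 has observed power of about one half, and larger p-values give less. It adds nothing to the test. A confidence interval shows which differences remain compatible with the data.

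**The case against.** Several points on the other side are sound.

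*The early stop was planned.* C closed under a pre-specified p<0.001 rule, and the Synopsis reports that the boundary was met. A reader might be tempted to recompute the antibody power at the closed size (23% for 58% v 65.5% and 37% for 58% v 68% at 124 v 124; 38% and 60% at 124 v 1000) and conclude that the trial lacks the power it states. The documents do not support that. Stopping early for efficacy does not lower a design's power, and power recomputed after rejection says nothing about the result.

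*The protocol admits weakness.* Section 11.1 does say underpowered, and calls the Arm 3 comparison exploratory. Both statements stand. But the first is made about Arm 1 versus Arm 2, and neither gives a detectable difference or an interval width for A versus B. Its stated reason, falling infection rates, would apply to A versus B as well, which strengthens the case for stating a range. Given these admissions and the open reporting of the closure, a reader should not infer that the ethics committee or the DSMB is misled.

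*The 1% is not the endpoint's rate.* It refers to B.1.351 alone in four districts, while the endpoint covers wild type and escape variants. This is correct, and it is why the A versus B figures are presented as assumptions. At higher risks the comparison is much more informative.

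*The choice of comparator size matters.* Two cases in 124 against none in 124 give p = 0.50, but against none in 1000 give p = 0.012. The latter mixes randomized and later non-randomized participants in A. The point made here does not depend on either figure.

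*The detail could go in a statistical analysis plan.* A full precision table could. But 11.1 is the protocol's own justification of size, and it currently justifies a different comparison.

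**Conclusion.** The point holds as a failure to update section 11.1, not as an arithmetic error. Every figure there reproduces, but only for 1000 in an arm that closed at 124. The antibody calculation is a valid rationale for the original design, and the interim result is untouched. It does not support recruiting up to 1000 each in A and B to compare infections, and nothing else in the protocol does so in numbers. The 10-to-0 scenario is obsolete: about 1.2 cases are expected in C at the plan's own rate.

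How informative A versus B would be depends on an unstated risk. At 1000 per arm a doubling has about 45% power from 1% and about 84% from 2.5%. These figures assume the risks shown, two-sided 5% testing and no dropout. They do not show that the comparison must fail, only that its worth ranges from poor to good and that the plan does not say where it expects to be.

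**What to change.** Amend section 11.1 in three places:

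- **(a)** Label the C versus A calculation as the rationale for the original design, give the actual numbers and the closure at the interim analysis, and withdraw the 10-to-0 scenario.
- **(b)** State for A versus B, at 1000 per arm, the detectable risk ratio or the expected confidence interval width over a range of assumed 180-day risks, for example 0.5% to 5%, and say that the risks are assumptions.
- **(c)** Replace the post-hoc power analysis with the confidence interval for the risk or rate ratio.

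The change is text only and needs no extra participants, visits or tests. Its cost is that the stated figures will look less favourable than the present ones.

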## 11.2 Randomization

Randomization of two of the study arms (group A and group C) will be performed in a 1:1 ratio stratified by 1) study site and 2) sex (male/female).

The randomization code will be generated by the study statistician using permuted blocks and implemented into the electronic CRF system (Askimed) in a two-step process using an external randomization tool or paper based. Patients will be randomized after verification of inclusion and exclusion criteria as well as stratification status and after screening assessments have been performed. Randomization code will be strictly blinded to clinical investigators and participants in Arms 1 and 2 for 90 days after the boost.

For the T cell determination sample, only participants from the Innsbruck trial site will be included to prevent poor cell quality due to sample transport. The first 100 samples at Innsbruck trial site in each of the three arms will be selected for T cell analysis.

Following the third immunization between day 200 and 260, 100 subjects will be selected for T cell analysis. Preferentially, subjects for which the T cell response had already been determined after boost immunization will be selected.

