### 11.3.5 Data Analysis

#### Efficacy analysis

Efficacy analyses are performed for the comparison of neutralizing titers against the wild type and escape variants at 30 days (primary endpoints of the study) and on breakthrough

infections of wild type/ escape variants (secondary endpoint) at 180 days. The main efficacy analysis is performed between the two randomized arms (Arm C: ChAdOx1-S prime & boost; Arm A: ChAdOx1-S prime and BNT162b2 boost).

Neutralising titer and breakthrough infection are both defined as binary quantitative variables.

Hypothesis testing between the two treatment arms will be performed using Chi testing and logistic regression including stratification variables.

Efficacy analyses will be performed on the ITT and PP populations. The analysis of the ITT population will be considered as the primary analysis. All statistical tests are two-sided with a significance level of 0.05.

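### Section 11.1 meets the admitted low power of the breakthrough-infection comparison with an undefined post hoc power analysis, which in its usual meaning only re-expresses the p-value

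*Protocol*

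**What the plan says.** Protocol section 11.1 sizes the trial on neutralising antibodies against B.1.351 and states that "we consider a sample size of n=1000 per study arm as appropriate". It then turns to breakthrough infection with B.1.351. From a regional count of 8 new cases a week it says "we expect 208 cases during the next 180 days", and scales this to about 10 cases per 1000 over 180 days. It works one scenario, 10 cases in Arm 1 (ChAdOx1-S twice) against none in Arm 2 (ChAdOx1-S then BNT162b2), and calls that split significant. Because infection rates were falling, it adds: "we would currently consider this an underpowered analysis and as such would perform a posthoc power analysis". It does not say which effect or event rate that analysis would use, or how its result would be read.

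Section 11.3.5 (Efficacy analysis) treats the endpoint as binary ("Neutralising titer and breakthrough infection are both defined as binary quantitative variables") and secondary, assessed at 180 days. It is analysed by chi-square "testing and logistic regression including stratification variables". It also says: "All statistical tests are two-sided with a significance level of 0.05".

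The Synopsis (Statistical methods & analyses) records that the homologous Vaxzevria arm was stopped and that the aim is now "to recruit up to 1000 participants in each of these two arms to analyse the number of breakthrough infections". Section 1.3 names the comparison this recruitment serves: homologous Comirnaty against heterologous. Section 4.1 gives 124 as the final size of the closed arm.

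**The concern.** A protocol that expects too few events has to say how a non-significant result will be read. The tool that section 11.1 names cannot help with that in its usual meaning. If power is computed at the observed effect, each p-value above 0.05 converts into a power below about one half. The label underpowered then attaches to every null result, including one from a large and informative data set.

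At stake is what can be said about protection against infection once the trial is over. A non-significant result is likely at the protocol's own event rate. Two regimens with equal risk, and two regimens of which one carries twice the risk, would receive the same label. The differences that the data exclude, which readers need to know, would not follow from the named analysis.

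**Working it through.** **Inputs.** From section 11.1: 8 cases a week, population 416,758, 5% detection, 1000 per arm. From section 11.3.5: two-sided alpha 0.05, chi-square test. From section 4.1: closed arm of 124. Halved and doubled risks, and an event rate of 0.5%, are illustrative assumptions.

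**1. The plan's own figures reproduce.** 8 × 26 weeks = 208 cases. 208 / 416,758 = 49.9 per 100,000. Dividing by 0.05 gives 998 per 100,000, about 10 per 1000. For 10/1000 v 0/1000, chi-square p = 0.0015 and Fisher p = 0.0019, so that split is significant as stated.

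**2. Observed power depends only on p.** Let z_p be the normal deviate of the two-sided p-value. Then observed power = Φ(z_p − 1.96) + Φ(−z_p − 1.96).

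| p | z_p | observed power |
|---|---|---|
| 0.05 | 1.960 | 50% |
| 0.10 | 1.645 | 38% |
| 0.20 | 1.282 | 25% |
| 0.50 | 0.674 | 10% |

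**3. Check on actual tables.** All 2×2 tables with 0 to 40 events per arm were enumerated, leaving out those with equal rates, and power at the observed rates was set against the chi-square p-value.

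- 1000 v 1000: the highest observed power among non-significant tables is 49.6% (23 v 38 cases, p = 0.051). The lowest among significant tables is 50.0%.
- 1000 v 124: the corresponding figures are 50.0% and 50.7%.

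The 50% line falls where the significance line falls, with or without the closed arm's reduced size.

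**4. More data do not change the label.** 100 v 90 cases with 1000 per arm gives p = 0.45 and observed power 12%. Yet the risk ratio is 1.11 with 95% CI 0.85 to 1.46, which excludes a 50% increase.

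**5. What an interval shows.** For the risk ratio, SE of the log = √(1/a − 1/n + 1/b − 1/n).

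- 10 v 10: √(0.099 + 0.099) = 0.445; RR 1.0, 95% CI 0.42 to 2.39.
- 10 v 8: RR 1.25, 0.50 to 3.15.
- 10 v 5: RR 2.0, 0.69 to 5.83.

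These are wide, and they say so. The 10 v 10 result has not excluded a doubling; the 100 v 90 result has.

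**6. Power for fixed effects, which can be stated in advance.** Exact binomial enumeration with the chi-square test, 1000 per arm:

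| relative reduction | event rate 1% | event rate 0.5% (assumed) |
|---|---|---|
| 100% | 99% | 74% |
| 75% | 57% | 31% |
| 50% | 24% | 13% |
| 25% | 9% | 6% |

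Fisher's test gives lower values (at 1%: 93%, 48%, 18% and 6%).

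**7. The comparison that section 11.1 discusses, at its present size.** With 124 in the homologous Vaxzevria arm the expected count at 1% is 124 × 0.01 = 1.24 cases. Power against 1000 heterologous participants for a halving is then about 17% by chi-square and 10% by Fisher.

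**The case against.** The strongest objection is that the term is undefined. Section 11.1 gives falling infection rates as its reason, so the uncertain input is the event rate. The authors may have meant to recompute power for a planned effect at the realised incidence, and that calculation would not restate the p-value. This stands: it cannot be said as fact that the planned analysis is observed power. But the protocol fixes no effect for such a calculation, and even then the answer would describe the design and not what the data rule out.

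Second, a reader might infer that the protocol uses post hoc power to rescue a null result. The text does not support that. It openly calls the analysis underpowered and nowhere says that the power figure will support a conclusion.

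Third, a reader might take the sentence to govern the comparison for which recruitment continues. Section 11.1 attaches it to Arm 1 v Arm 2 for B.1.351 and calls the comparison with the Comirnaty arm exploratory and descriptive. The Synopsis and section 1.3 describe continued recruitment without mentioning a power analysis. The extension is an inference, though section 11.1 holds the only power statement for this endpoint.

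Fourth, the lack of a stated interval is not a fault in itself. That is commonly left to a statistical analysis plan, and logistic regression software gives an interval for the odds ratio as standard. This also stands. The defect is the analysis that is named.

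**Conclusion.** The point holds in a limited form and is worth acting on. Section 11.1 commits to an undefined post hoc power analysis as its response to admitted low power. Read in the usual sense, it adds nothing to the p-value, and every non-significant result falls below about 50%. Read as power for a fixed effect at the realised rate, it is not circular, but it still does not show which differences the data exclude.

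The point matters because a null result is likely: at the protocol's 1% rate with 1000 per arm, chi-square power is about 24% for a halving and 57% for a 75% reduction. These figures assume full recruitment and no dropout, since the protocol gives no dropout figure. The endpoint is secondary. The primary analysis, the planned tests and the significance level are untouched.

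**What to change.** Delete the post hoc power clause from section 11.1 and state in its place:

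- Breakthrough infection is reported as a risk difference with a 95% score or exact confidence interval, chosen in advance. Such an interval still works when an arm has no cases, where a risk ratio fails. For 10 v 0 with 1000 per arm, the Wilson limits are 5.4 to 18.3 and 0 to 3.8 per 1000. The Newcombe interval for the difference is then 10 − √((10 − 5.4)² + 3.8²) to 10 + (18.3 − 10), or about 4.0 to 18.3 per 1000.
- The odds ratio with its interval from the planned stratification-adjusted logistic regression is added where it can be estimated.
- A non-significant result is interpreted by the differences the interval excludes and not as evidence of equal protection.
- The non-randomised comparison with the Comirnaty arm is descriptive and open to confounding.

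If a power statement is kept, give it in advance for fixed effects over a range of event rates, as in step 6, and use the actual size of the closed arm wherever that arm is compared.

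The cost is a few sentences and slightly more reporting, with no new data and no change to alpha. The intervals will be wide, and that will be visible.
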